## Methods

### Design

This manuscript introduces a study design and uses a mixed methods approach. The study includes assessment of direct observational, utility, and usability study designs. Surveys, interviews, semipredefined tasks, and capturing screen activities are also utilized. The modified Delphi method is also used in the study.

### Ethics Approval

The study has been approved by the Institutional Review Board (IRB) of Clemson University, South Carolina (IRB2020-056).

### Participants and Recruitment

Experienced and inexperienced clinical researchers, and a panel of clinical research experts, have been recruited for this study. The primary criterion used to distinguish subjects in the 3 groups is the level of their experience in clinical research. Table 1 summarizes the requirements for clinical researchers, expert panel members, and the computers that clinical researchers use during the study sessions. Participants are compensated for their time according to professional organization guidelines.

**Table 1 table1:** Summary of the criteria for study participants and clinical research expert panel members.

Variable	Inexperienced clinical researchers^a^	Experienced clinical researchers^a^	A panel of clinical research experts
Participation in research hypothesis generation and study design	≤2 years	Leading role ≥5 and <10 years	Leading role ≥10 years
Participation in data analysis of study results	≤2 years	Leading role ≥5 and <10 years	Leading role ≥10 years
Publications in clinical research	Not required	≥5 as a leading author, including first, correspondence, or senior author for original studies	≥10 as a leading author, including at least one article in a high-impact journal in the past 5 years
Review experience in clinical research for conferences, journals, or grants	Not required	Not required	≥10 years
Internet connection	Required	Required	Required
Microphone	Required	Required	Not required
Software package for data analysis (eg, Microsoft Excel and R)	Required	Required	Not required
Tools to facilitate research hypothesis generation, if available	Required	Required	Not required

^a^If a participant has clinical research experience between 2 and 5 years, the decisive factor for the experienced group will be 5 publications for original studies as the leading author.

To recruit participants, invitational emails and flyers have been sent to collaborators, along with other communication means, including mailing lists, such as those of working groups of the American Medical Informatics Association, South Carolina Clinical & Translational Research Institute newsletters, and PRISMA health research newsletters, and Slack channels, such as National COVID Cohort Collaborative communities. All study sessions are conducted remotely via video conference software (Webex, Cisco) and recorded via a commercial software (BB FlashBack, Blueberry Software).

### Introduction to VIADS

In this study, we have used VIADS as an example of a secondary data analytics tool. VIADS is a visual interactive analytical tool for filtering and summarizing large health data sets coded with hierarchical terminologies [22,23,35]. It is a cost-free web-based tool available for research and educational purposes. VIADS can be used by both registered users and guest users without registration. VIADS and the underlying algorithms were developed previously by the authors [20,21,24]. VIADS was designed to use codes and usage frequencies from terminologies with hierarchical structures to achieve the following objectives: (1) provide summary visualizations, such as graphs, of data sets; (2) filter data sets to ensure manageable sizes based on user selection of algorithms and thresholds; (3) compare similar data sets and highlight the differences; and (4) provide interactive, customizable, and downloadable features for the graphs generated from the data sets. VIADS is a useful secondary data analytics tool that can facilitate decision-making by medical administrators, clinicians, and clinical researchers. For example, VIADS can be used to track longitudinal data of a hospital over time and can explore trends and detect diagnosis trends and differences over time. VIADS can also be used to compare 2 similar medications and the medical events associated with the medications in order to provide detailed evidence to guide more precise clinical use of the medications [20]. This study provides evidence of the different information needs of physicians and nurses via the algorithms of VIADS [21]. Figure 1 shows example screenshots of VIADS.

Meanwhile, we recognize that VIADS can only accept coded clinical data and their associated use frequencies. Currently, VIADS can accept data sets coded using ICD9-CM, ICD10-CM, and MeSH. This can limit the types of scientific hypotheses generated by VIADS.

**Figure 1 figure1:**
[figure not shown]
Selected screenshots of VIADS. (A) Homepage; (B) validation module; (C) dashboard; (D) a graph coded using International Classification of Diseases, 9th Revision-Clinical Modification (ICD9-CM) codes and generated by VIADS.

### Preparation of Test Data Sets

We have prepared and used the same data sets for this study across different groups in order to reduce the potential biases introduced by different data sets. However, all data sets (ie, input files) used in VIADS are generally prepared by users within specific institutions. Table 2 summarizes the final format of data sets and the minimum acceptable sizes of data sets needed for analysis in VIADS. The current version of VIADS is designed to accept all data sets coded by the 3 types of terminologies (ICD9-CM, ICD10-CM, and MeSH) listed in Table 2. No identified patient information is included in the data sets used in VIADS, as the data sets contain only the node identification (ie, terminology code) and usage frequencies.

**Table 2 table2:** Acceptable formats and data set sizes in VIADS.

Data set^a^ and graph node ID (code)		Usage frequency
**ICD9-CM^b^ data set**		
	300.00	2223
	278.00	5567
	… …^c^	…
**ICD10-CM^d^ data set**		
	O10.01	5590
	E11.9	50,000
	… …^c^	…
**MeSH^e^ data set**		
	A0087342	16,460
	A0021563	4459
	… …^c^	…

^a^Acceptable data set sizes for Web VIADS are as follows: patient counts ≥100 and event counts ≥1000.

^b^ICD9-CM: International Classification of Diseases, 9th Revision-Clinical Modification.

^c^There are many more codes in addition to the 2 examples provided.

^d^ICD10-CM: International Classification of Diseases, 10th Revision-Clinical Modification.

^e^MeSH: Medical Subject Headings.

The usage frequencies of the data sets used in VIADS can be either of the following: patient counts (the number of patients associated with specific ICD codes in the selected database) or event counts (the number of events [ICD codes or MeSH terms] in the selected database).

An ancestor-descendant table, which contains 1 row for each node and each of its distinct descendants, can calculate class counts easier and more accurately without counting the same node multiple times. These implementation details have been discussed in greater detail in prior publications [20,21].

A publicly accessible data source [36], including ICD9-CM codes, has been used to generate the needed input data sets. The patient counts are used as frequencies. Although ICD10-CM codes are now used in the United States, ICD9-CM data spanning the past several decades are available in most institutions across the country. Therefore, ICD9-CM codes have been used to obtain historical and longitudinal perspectives.

### Instrument Development

Metrics have been developed to assess research hypotheses generated during the study sessions. The development process goes through iterative stages (Figure 2) via Qualtrics surveys, emails, and phone calls. First, a literature review is conducted to outline draft metrics. Then, the draft metrics are discussed and iteratively revised until all concerns are addressed. Next, the revised metrics are distributed to the entire research team for feedback. The internal consensus processes follow a modified Delphi method [37]. Modifications at this point primarily include transparent and open discussions conducted via email among the research team and anonymous survey responses received before and after discussions. The main difference between our modification and the traditional Delphi method is the transparent discussion among the whole team via emails between the rounds of surveys.

**Figure 2 figure2:**

Development process for metrics to evaluate research hypotheses in clinical research.

The performance of scientific hypothesis–generation tasks will be measured using metrics that include the following qualitative and quantitative measures: validity, significance, clinical relevance, feasibility, clarity, testability, ethicality, number of total scientific hypotheses, and average time used to generate 1 scientific hypothesis. In an online survey, the panel of clinical research experts will assess the generated research hypotheses based on the metrics we have developed.

A survey (Multimedia Appendix 1) is administered for the first 4 groups at the end of the research hypothesis–generation study sessions (Figure 3). The groups that use VIADS also complete a modified System Usability Scale (SUS) questionnaire (Multimedia Appendix 2) evaluating the usability and utility of VIADS. The follow-up or inquiry questions and parameters generated during the think-aloud process used in Study 1 (Figure 3) are as follows:

What are the needed but currently unavailable attributes that would help clinical researchers generate research hypotheses? The question is similar to a wish list of features facilitating research hypothesis generation.Follow-up questions clarify potential confusion during the think-aloud processes or enable meaningful inquiries when unexpected or novel questions emerge during observations [38]. However, these questions have been kept to a minimal level to avoid interrupting clinical researchers’ thinking processes. This method complements the data from the think-aloud video captures.Can the list of items in Multimedia Appendix 3, which has been compiled from traditional clinical research textbooks [1-3,8,39] on scientific hypothesis generation and research question formulation, facilitate clinical researchers’ research hypothesis generation when guided by secondary data analysis?

A survey will be developed based on the comparative results of the first 4 groups and administered at the end of Study 2. The identified differences from Study 1 will be the focus of the survey to determine whether these differences are helpful in Study 2.

**Figure 3 figure3:**
[figure not shown]
Summary of the study procedures. Blue boxes indicate data collected in Study 1.

### Study Design

Study 1 tests all 3 study hypotheses. If the study hypotheses are supported in Study 1, we will conduct a follow-up study (Study 2) to examine whether and how the efficiency or quality of research hypothesis generation may be improved or refined.

We will use the think-aloud method to conduct the following tasks: (1) observe the research hypothesis–generation process; (2) transcribe data, and analyze and assess if VIADS [22] and different levels of experience of clinical researchers influence the process; and (3) assess the interactions between VIADS (as an example of a secondary analytical tool) and the experience levels of the participants during the process. Figure 3 summarizes the Study 1 and Study 2 procedures.

#### Study 1

Experienced and inexperienced clinical researchers conduct research hypothesis–generation tasks using the same secondary data sets. The tasks are captured to describe participants’ research hypothesis–generation processes when guided by analysis of the same data sets. VIADS is also used as an example of a secondary data analytics tool to assess participants’ research hypothesis–generation processes. Accordingly, 2 control groups do not use VIADS, while 2 intervention groups do use it.

A pilot study, Study 0, was conducted in July and August 2021 for each group to assess the feasibility of using the task flow, data sets, screen capture, audio and video recordings, and study scripts. In Study 1, 4 groups are utilized. Table 3 summarizes the study design and participants in each group. The 4 groups will be compared in order to detect the primary effects of the 2 factors and their interactions after completing Study 1. After recruitment, the participants are separated into experienced or inexperienced groups based on predetermined criteria. Then, the participants are randomly assigned to a group that uses VIADS (3-hour session, with 1 hour to conduct VIADS training) or does not use VIADS (2-hour session) via block randomization.

**Table 3 table3:** Design of Study 1 for assessment of the hypothesis–generation process in clinical research.

Variable	Number of experienced clinical researchers	Number of inexperienced clinical researchers
Not using VIADS	8 (Group 1)	8 (Group 2)
Using VIADS	8 (Group 3)	8 (Group 4)

We conduct 1 study session individually with each participant. The participants are given the same data sets from which to generate research hypotheses with or without VIADS during each study session. The same researcher observes the entire process and captures the process via think-aloud video recordings. Follow-up or inquiry questions from the observing researcher are used complementarily during each study session. The study sessions are conducted remotely via Webex. All screen activities are captured and recorded via BB FlashBack [40].

#### Study 2

If the results of Study 1 indicate group differences as expected (in particular, differences are found between experienced and inexperienced clinical researchers, along with differences between groups using VIADS and not using VIADS), Study 2 will be conducted to examine whether the efficiency of the research hypothesis–generation process could be improved. Specifically, we will analyze for group differences, identify anything related to VIADS, and incorporate them into VIADS. Then, we will test whether the revised and presumably improved VIADS increases the efficiency or quality of the research hypothesis–generation process. In this process, the group that has the lowest performance in Study 1 will be invited to use the revised VIADS to conduct research hypothesis–generation tasks again with the same data sets. However, at least 8 months will be allowed to pass in order to provide an adequate wash-out period. This group’s performance will be compared with that in Study 1.

If no significant difference can be detected between the groups using VIADS and not using VIADS in Study 1, we will use the usability and utility survey results to revise VIADS accordingly without conducting Study 2. If no significant difference can be detected between experienced and inexperienced clinical researchers, Study 2 will recruit both experienced and inexperienced clinical researchers as study participants. In this case, Study 2 will focus only on whether a revised version of VIADS impacts the research hypothesis–generation process and outcomes.

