### Data and Statistical Analysis

While conducting the given tasks, the qualitative data collected via the think-aloud method will be transcribed, coded, and analyzed according to the grounded theory [41,42], a classical qualitative data analysis method. This data analysis has not begun yet because data are still being collected. Combined analysis of discourse [30], video recordings of the study sessions, and screen activities will be conducted. The main components or patterns that we will focus on during analysis include potential nonverbal steps, sequential ordering among different components (such as prioritization of the use of either experience or data) across groups, seeking and processing evidence, analyzing data, generating inferences, making connections, formulating a hypothesis, searching for information needed to generate research hypotheses, and so forth. Ideally, based on video analyses and observations, we plan to develop a framework for the scientific hypothesis–generation process in clinical research, which is guided by secondary data analytics. Similar frameworks exist in education and learning areas [43], but do not currently exist in the field of clinical research.

The outcome variable used is based on the participants’ performance in research hypothesis–generation tasks. The performance is measured by the quality (eg, significance and validity) and quantity of the research hypotheses generated through the tasks and the average time to generate 1 research hypothesis. At least three clinical research experts will assess each hypothesis using the scientific hypothesis assessment metrics that were developed for this study. The metrics include multiple items, each on a 5-point Likert scale. The details of the metrics are described in the Instrument Development section.

The data will be analyzed with a 2-tailed factorial analysis. We calculated the required sample size in G*Power 3.1.9.7 for a 2-way ANOVA. The sample size was 32 based on a confidence level of 95% (α=.05), effect size f=0.5, and power level of 0.8 (β=.20).

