In Study 1, we will use descriptive statistics to report how many hypotheses were generated, average time spent per hypothesis, and how many hypotheses were evaluated for each participant. A 2-way ANOVA will be used to examine the main effects of VIADS and experience, as well as the interaction effect of the 2 factors. In the ANOVA, the outcome variable is the expert evaluation score. The follow-up survey data will be analyzed using correlations to examine the relationship between participants’ self-rated creativity, the average time per hypothesis generation, the number of hypotheses generated, and the expert evaluation score. The SUS will be used to assess the usability of VIADS. Qualitative data from the SUS surveys will be used to guide revisions of VIADS after Study 1. Descriptive statistics will also be used to report the answers to other follow-up questions.

A *t* test will be conducted to determine whether the revised VIADS improves the performance of research hypothesis generation in Study 2.

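### Study 2 re-tests the lowest-scoring Study 1 group against itself with no concurrent control, so it cannot isolate the effect of revising VIADS

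*Protocol article*

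**What the plan says.** Study 1 is a 2×2 design with 8 people per group (Study Design, Table 3). In it, "2 control groups do not use VIADS, while 2 intervention groups do use it". Groups 1 and 2 are the experienced and inexperienced researchers without VIADS; Groups 3 and 4 are the corresponding groups with it.

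Study 2 follows "If the results of Study 1 indicate group differences as expected", which that subsection explains as differences on both experience and VIADS use. Then "the group that has the lowest performance in Study 1 will be invited to use the revised VIADS" on the same data sets, and this group's "performance will be compared with that in Study 1". On timing, "at least 8 months will be allowed to pass in order to provide an adequate wash-out period". Under Data and Statistical Analysis, a *t* "test will be conducted to determine whether the revised VIADS improves the performance of research hypothesis generation in Study 2". No concurrent arm, and no arm on the unrevised tool, is described. If Study 1 shows no VIADS difference, Study 2 is not run.

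**The concern.** The t test is given one job: to show whether the revised VIADS improves performance. A before-after change in one selected group contains several other things:

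- the effect of having VIADS at all, if the group did not use it in Study 1;
- practice, because the data sets are the same;
- time, because 8 months is a third of the 2-year ceiling that defines an inexperienced researcher in Table 1 (8/24);
- selection of the group for its low score.

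Nothing in the design separates these from the revision. The first is the most serious. If the lowest group had no VIADS, the benefit of the original tool, which Study 1 would just have shown, is credited to the revision. A revision of no value could then be reported as a success.

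**Working it through.** **The plan's own figure.** The plan states "The sample size was 32 based on a confidence level of 95% (α=.05), effect size f=0.5, and power level of 0.8 (β=.20". With two levels, f=0.5 is a standardised difference d=2f=1.0. The normal approximation gives 2(1.96+0.842)²/1.0² = 15.7, so 16 per level and 32 in total, which reproduces the figure. The noncentral F calculation gives power 0.78 at 32 and needs 34 for 0.80. This does not affect the point; it supplies the effect size of 1 SD used below.

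**Inputs from the protocol article.** 8 per group; two-sided α=0.05; Study 2 triggered when both main effects are significant; lowest observed group mean selected; same people re-tested.

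**Assumptions, because the article gives no figure.** Experience effect 1 SD; test-retest correlation r from 0.3 to 0.7; practice gain 0 or 0.5 SD; paired analysis; revision effect over the original VIADS exactly zero.

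**Step 1: which group is lowest?** In simulated Study 1 data, among triggered studies:

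| True VIADS effect | Lowest group had no VIADS |
|---|---|
| +1.0 SD | 99.7% (Group 2: 99.3%) |
| +0.5 SD | 98.9% |
| 0 | about 52% |
| −0.5 SD | 1.1% |
| −1.0 SD | 0.4% (Group 4: 99.2%) |
| +1.5 SD experienced, −0.5 SD inexperienced | 51% |

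The answer therefore turns on the direction of the VIADS effect.

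**Step 2: VIADS helps by 1 SD and the revision adds nothing.** Group 2 moves from no tool to a tool worth 1 SD. The SD of a within-person change is √(2(1−r)). At r=0.5 this is 1.0, so the noncentrality is 1.0×√8 = 2.83 against a critical value of 2.365 on 7 df, and the test is significant in 68% of cases before the trigger and selection are taken into account. With both included, simulation gives 63% at r=0.3, 82% at r=0.6 and 90% at r=0.7. The mean change is a little over 1 SD.

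**Step 3: VIADS lowers scores by 1 SD and the revision adds nothing.** Group 4 is re-tested with an equivalent tool. The test declares improvement in about 3% of runs without practice. With a 0.5 SD practice gain it does so in 23% (r=0.3), 33% (r=0.6) and 40% (r=0.7).

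**Step 4: regression to the mean.** After the trigger, with 1 SD effects, the selected group's mean is about 0.13 SD below its true value. The expected rebound is 0.13×(1−r): 0.09 SD at r=0.3 and 0.04 SD at r=0.7.

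**The case against.** The strongest reply is that the protocol does not fix the direction of the VIADS effect. The study hypothesis in the Introduction says only that results will differ, and "The data will be analyzed with a 2-tailed factorial analysis". Initial Observations reports that VIADS training raised cognitive load and draws no conclusion. Significance of the Study does anticipate that such tools help, but an expectation is not a result. A reader might infer that the re-tested group will almost surely be one without VIADS. Step 1 shows that this holds only if VIADS helps without a qualitative interaction. The opening of Study Design also makes Study 2 depend on all the study hypotheses, including the interaction, and this sits uneasily with the purely additive effects assumed above.

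A reader might also infer that regression to the mean alone would create a large spurious gain. It would not. Large values arise only when all groups are truly equal and no trigger is applied, and in that setting Study 2 would mostly not run. The practice gain is an assumption throughout.

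The aim could also be read as revised VIADS against no tool, in which case the gain in Step 2 is partly a real tool effect. But Study 1 would largely have answered that question already, and the comparison would still be uncontrolled. The article also plans a Study 2 survey on whether the differences identified in Study 1 are helpful, so the t test is not the only evidence, although a survey is not a control. The wash-out period may limit carry-over, but it cannot show that carry-over is absent.

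These replies make the size of the problem conditional. They do not supply a comparator.

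**Conclusion.** The concern holds in conditional form. Whichever group is lowest, the planned test cannot attribute a change to the revision.

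- **If VIADS helps by about 1 SD, as the authors anticipate**, with experience also worth 1 SD and no qualitative interaction, the comparison is revised VIADS against no tool in about 99% of triggered studies. A worthless revision is then declared an improvement in about 63% to 90% (r=0.3 to 0.7).
- **If VIADS lowers scores**, the comparison is revised against original VIADS, and what remains is practice and time: false improvement in about 3% without practice, and 23% to 40% with an assumed 0.5 SD gain.

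The unconditional claim that a useless revision would usually be declared a success is not supported, since it rests on the first scenario. The severity is moderate: Study 1 carries the three study hypotheses, and Study 2 is a conditional follow-up that has not started.

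**What to change.** Drop the rule that selects the lowest-performing group, and state the comparator as the original VIADS.

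**Minimum.** Re-invite a group that used the original VIADS in Study 1 (Group 3 or 4), name the paired t test, and report the result as uncontrolled for practice and time. Group 4 is the realistic choice, since only one experienced researcher had volunteered (Lessons Learned). This needs protocol wording, an IRB amendment and no extra sessions. With 8 people, 80% power requires a standardised within-person change of 1.16.

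**Preferred.** Re-invite Groups 2 and 4 (16 people; 16 inexperienced sessions are reported complete under Recruitment). Randomise 1:1 to original or revised VIADS within Study 1 arm, and compare by ANCOVA on the Study 1 score. Practice, time and selection then fall equally on both arms in expectation. The cost is about 8 more repeat sessions, plus at least three expert ratings for each added hypothesis, when experts have been hard to recruit. Power is limited: 8 per arm detects about 1.51 SD unadjusted, or 1.51×√(1−0.5²) = 1.31 SD with adjustment at r=0.5. Report the result as an estimate with a confidence interval rather than as a pass-or-fail test.
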